#### Number of subjects and statistical power

To establish the non-inferiority (one-sided equivalence) of the 400 μg misoprostol (sublingual or vaginal) regimen compared to the 800 μg with respect to efficacy, we require the upper limit of the one-sided 95% confidence interval (or the two-sided 95% confidence interval) for a difference in complete abortion rates (that of 800 μg minus that of 400 μg) to be within a margin of equivalence of 3%. It is estimated that if the abortion rates in the two regimens are both equal to 95%, about 680 subjects will be required in each group to demonstrate non-inferiority with a power of 80%, i.e. a total of about 2720 subjects. To allow for a 5% of women lost to follow-up or with undetermined outcomes, then about 720 women will have to be recruited per group, a total of about 2880. If 15 centres participate in the study, 192 subjects will be needed in each centre. However, to ensure recruitment in one year time, we plan to include one additional centre, 16 centres in all. Since we plan to take four packs per centre for quality control, the actual number of women recruited per centre will be 188. These calculations allow for the presence of an interaction between misoprostol dose and its route of administration.

For the choice of the non-inferiority margin, a clinical criterion was used, not a statistical one. This is based on the fact that there are not placebo-controlled trials available and the efficacy of placebo would be close to zero. We set the margin at 3% based on clinical assessment that this difference is not relevant.

It is estimated that the trial will require 12 to 14 months for data collection at each centre and between 6 and 12 months of centralized data analysis in Geneva.

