The results of our recent study [13] demonstrate an equivalent efficacy for both 24 h and 48 h intervals when 800 μg misoprostol is administered vaginally after mifepristone. As 24 h interval is more practical it is likely to become the standard in mifepristone-misoprostol regimens. This is why we chose the 24 h interval for the present trial.

The ultimate goal of our research is to improve the methods for termination of early pregnancy. The main objective of the present randomized trial is to compare four misoprostol regimens when administered either sublingually or vaginally 24 hours after 200 mg of mifepristone, among women with a gestational age of up to 63 days. The four regimens will be compared in respect of the following main outcomes: (i) their efficacy to induce complete abortion; (ii) induction-to-abortion interval, when possible; (iii) the occurrence of side-effects; and (iv) women's perceptions.

Although there are no comparative studies the efficacy might be somewhat lower if the dose of misoprostol is reduced. If, however, the side-effects will decrease and the regimen is more acceptable to women, it would be justified to use a lower dose if non-inferiority is demonstrated within a margin of 3%. Our hypothesis is that the efficacy of 400 μg misoprostol, whether given sublingually or vaginally after mifepristone pretreatment, is not inferior to that of 800 μg misoprostol within a margin of 3%.

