### Data management

Participating centres will be requested to record the data on paper data collection forms, enter them and send them electronically on a weekly basis to Geneva, using a Web-based system [14]. Recruitment and data quality will be monitored by the Programme's Statistics and Informatics Services Team using this system.

Data will be analyzed centrally in Geneva. Descriptive statistics will be calculated for all baseline characteristics for all subjects randomized, by treatment group, to describe characteristics of the population and to assess comparability of the groups. The overall summary statistics for women who complete the trial will be compared with those for the subjects lost to follow-up.

All subjects randomized having known outcome will be included in the main efficacy analysis in their randomized groups. If attempts fail to locate and contact a woman lost to follow-up, and her outcome of treatment is not known, then that woman will be excluded from the efficacy analysis. If she has information on side effects, she will be included in the safety analysis. Baseline characteristics of women lost to follow-up will be compared with those completing the study and between groups, to explore the possibility of bias due to these differences.

Crude rates for each outcome will be calculated in each arm and exact confidence intervals based on the binomial distribution calculated as described in Armitage and Berry [15]. If the interaction of misoprostol route by misoprostol dose is significant at 5% level, comparisons will be made between routes for each dose and between doses for each route. If the interaction is not significant at 5%, two comparisons will be made, between routes for the two doses combined, and between doses for the two routes combined. For these comparisons, relative risks (RR) of failure to achieve a complete abortion and failure to terminate pregnancy and the two-sided 95% CIs will be calculated by standard methods, as well as risk differences and two-sided 95% CIs. The latter will be used to test the non-inferiority hypotheses (at 2.5% level of significance) for achieving complete abortion.

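### The stated 80% power holds for one route taken singly at one-sided 5%; at the 2.5% level the plan tests, it is about 72% per route and, if both routes must succeed, about 52%

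*Protocol article*

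**What the plan says.** All references are to the protocol article.

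- **Hypothesis (Background).** It is that "the efficacy of 400 μg misoprostol, whether given sublingually or vaginally after mifepristone pretreatment, is not inferior to that of 800 μg misoprostol", with a 3% margin.
- **Sample size (Number of subjects and statistical power).** The criterion is that the upper limit of the "one-sided 95% confidence interval (or the two-sided 95% confidence interval") for the 800 μg minus 400 μg difference has "to be within a margin of equivalence of 3"%. With 95% complete abortion in both regimens, "about 680 subjects will be required in each group to demonstrate non-inferiority with a power of 80"%. The total is given as about 2720, which is four groups of 680, so a group is one dose-by-route cell. Allowing for 5% loss gives about 720 per group. The paragraph ends: "These calculations allow for the presence of an interaction between misoprostol dose and its route of administration".
- **Analysis (Data management).** "If the interaction of misoprostol route by misoprostol dose is significant at 5% level, comparisons will be made between routes for each dose". The two doses are then likewise compared separately by route. Otherwise doses are compared with the routes combined. On the two-sided 95% intervals for risk differences it says: "The latter will be used to test the non-inferiority hypotheses (at 2.5% level of significance) for achieving complete abortion".

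**The concern.** The interaction sentence follows directly on the 80% figure, so a reader will take 80% as the power of the dose comparison when an interaction is present. Three features of the calculation limit what that figure covers.

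1. It is the power of one two-arm comparison. When routes are analysed separately there are two such comparisons, and the hypothesis speaks of both routes.
2. It assumes the same rate at both doses. A true interaction on the risk-difference scale means that the dose difference is not zero in at least one route, so the assumption cannot hold in both.
3. It corresponds to one-sided 5%, whereas the analysis tests at 2.5%.

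At stake is how a within-route result is read. Someone who believes that each route had 80% power, or that both together did, may give too much weight to a failure to show non-inferiority in one route.

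**Working it through.** **Inputs.** Rates 95% and 95%, margin 0.03, power 80%, 680 per cell and 5% loss come from Number of subjects and statistical power. The 2.5% test level comes from Data management. Planned recruitment is 188 × 16 = 3008, or 752 per cell if the four groups are equal in size. Less 5%, 752 × 0.95 ≈ 714 are evaluable.

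**Reproducing 680.** For a risk difference with unpooled variance:

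n = (z_α + z_0.80)² × 2 × 0.95 × 0.05 / 0.03²

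- One-sided 5%: (1.645 + 0.842)² × 0.095 / 0.0009 ≈ 653. With the restricted-likelihood (Farrington-Manning) variance: 683.
- One-sided 2.5%: (1.960 + 0.842)² × 0.095 / 0.0009 ≈ 829. With Farrington-Manning: 869.

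So 680 matches one-sided 5% (683, 0.4% off) and neither 2.5% figure.

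**Power of one within-route comparison.** Power = Φ(0.03 / √(0.095/n) − z_α).

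- n = 680: 0.03/0.01182 = 2.538. At 5%, Φ(2.538 − 1.645) = 0.814. At 2.5%, Φ(2.538 − 1.960) = 0.718.
- n = 714: 0.03/0.01153 = 2.601. At 5%, 0.830. At 2.5%, 0.739.

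**Both routes.** The two comparisons use different women, so the powers multiply; for example, 0.814² = 0.663 and 0.718² = 0.516.

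**Routes pooled.** The same formula applies with twice the cell size per dose, 1360 or 1428.

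| Comparison, no true dose difference | Evaluable per cell | One-sided 5% | One-sided 2.5% |
|---|---|---|---|
| One route | 680 | 81% | 72% |
| One route | 714 | 83% | 74% |
| Both routes | 680 | 66% | 52% |
| Both routes | 714 | 69% | 55% |
| Routes pooled | 680 | 97% | 95% |
| Routes pooled | 714 | 98% | 96% |

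A simulation of 500,000 trials at 680 per cell gave 0.814 for one route and 0.663 for both at one-sided 5%, and 0.721 and 0.520 at 2.5%.

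**A true dose difference in one route (assumed, since the document gives none).** Suppose 400 μg gives 94% against 95% in one route, well inside the margin. The standard error at 680 is √((0.0475 + 0.0564)/680) = 0.01236, and the distance to the margin is 0.02. Power for that route is Φ(1.618 − 1.645) = 0.49 at 5% and Φ(1.618 − 1.960) = 0.37 at 2.5%. If 400 μg is instead 1 point better in one route and equal in the other, joint power at 680 rises to about 79% at one-sided 5% (0.814 × 0.972) and 68% at 2.5% (simulated).

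**What the cell size does provide.** Powering only the pooled comparison at one-sided 5% would need 653/2 ≈ 327 per cell. The planned 680 is about twice that.

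**The case against.** The strongest reply is that the interaction sentence is defensible. Giving every cell the full two-arm size is the usual way to allow for an interaction in a factorial trial, and here it roughly doubles the trial compared with powering the pooled comparison alone. A reader might infer that the design makes no allowance for an interaction and that the sentence should be deleted. The document does not support that: each route keeps its own planned comparison, and the sentence explains the trial's size.

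A reader might also infer that both routes must succeed, so that power is about 66% at best. That does not stand either. The Background wording, "whether given sublingually or vaginally after mifepristone pretreatment, is not inferior", can be read as one claim over both routes or as one claim per route. Neither the analysis text nor the sample-size text sets a joint criterion or promises 80% joint power. Nor is 66% a ceiling: at one-sided 5% planned recruitment gives 69%, or 72% with no loss (0.847²), and an interaction that favours 400 μg in one route gives about 79% at 680.

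It is fair, too, that equal rates are a normal planning assumption for non-inferiority, and that any such design loses power when the new regimen is truly somewhat worse. That explains the assumption, but it does not remove the need to state it beside a claim about interaction, particularly as the Background itself expects that efficacy might be somewhat lower at the reduced dose.

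What the reply leaves untouched is the test level. Even one route, with no dose difference, does not reach 80% at the 2.5% level that the analysis applies.

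**Conclusion.** The power statement is wrong as written for the test the plan specifies, and incomplete as a statement about interaction. The 80% is right for one route taken singly, at one-sided 5%, with no dose difference in that route. At 2.5% the figure is about 72% at 680 evaluable per cell and 74% at 714. On the reading that the hypothesis needs both routes, which is an inference from the Background, joint power is about 66% at one-sided 5% and 52% at 2.5% (69% and 55% at 714). With 400 μg 1 point worse in one route, that route has 49% or 37% at 680.

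These figures assume 95% complete abortion otherwise, equal cells, normal-approximation risk-difference intervals, and within-route tests considered without conditioning on the interaction test. The pooled comparison is well powered at either level. The defect therefore lies in what is claimed for the within-route comparisons; it is not a reason to call the design unsound.

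**What to change.** In Number of subjects and statistical power, keep the interaction sentence and qualify it: the group size gives each route its own dose comparison, and the stated power refers to one route singly, assuming no dose difference in that route. Then replace the single 80% with power at the 2.5% level actually tested:

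- each route singly: about 72% (680 evaluable per group) to 74% (714);
- non-inferiority in both routes: about 52% to 55%;
- doses compared with routes combined: about 95%.

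Say that each figure assumes no true dose difference in the routes concerned. Say also whether the hypothesis is one claim covering both routes or a separate claim for each, so that the reader knows which figure applies.

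This changes wording only. It needs no extra women and no change of design. The cost is a less favourable stated power for the within-route comparisons.

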#### Project management

The trial will be conducted in 16 collaborating centres under the supervision of a principal investigator in each centre. The responsibilities of principal investigators are described in the "Guidelines for Investigators" for this project. Overall co-ordination of the project will be the responsibility of the Manager and statistical staff of the Programme's Group for Research on Post-ovulatory Methods for Fertility Regulation. This responsibility will include, inter alia, the organization and supervision of the trial, communication with the principal investigators, and the analysis and writing-up of the results.

This trial will be funded by the Packard Foundation and the UNDP/UNFPA/WHO/World Bank Special Programme of Research, Development and Research Training in Human Reproduction, Department of Reproductive Health and Research, World Health Organization.
